### Study objectives and endpoints

The primary endpoint is the amount of administered iodinated contrast agent (mL). The intra-arterial iodinated contrast agents Ultravist (300 mg/mL; Bayer Vital, Leverkusen, Germany) and Xenetix (300 mg/mL; Guerbet, Roissy, France) will be used during all interventions of the Maastricht University Medical Center (MUMC) and St. Antonius Hospital (SAH), respectively.

Secondary endpoints are the following:Technical success of the procedure, defined as < 30% trans-lesion residual stenosis and no flow-limiting dissections;Fluoroscopy time from the start to end of the procedure in minutes and seconds;Overall procedure time, defined as the time from femoral access to arterial closure (minutes);Radiation dose as dose area product (DAP) in mGycm^2^ from the start to the end of the procedure;Fusion accuracy between the overlaid MRA and DSA, categorized as accurate (< 2 mm), mismatch (2–5 mm), or inaccurate (> 5 mm);Complications that occur during the intervention and before discharge.

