### Randomization

Randomization will be performed by the investigators with the use of an automated web-based randomization and electronic data capture software (MACRO 4.6.0, https://ecrf.ctcm.nl/macro). Randomization will be performed according to minimization; for a difference of 2 between the two groups (control and study group), there is a 90% chance that the next individual will be allocated to the group with the smallest number of patients. Stratification factors are the site (MUMC or SAH), weight (≤ 90 or > 90 kg), and estimated glomerular filtration rate (eGFR) (≤ 60 or > 60 mL/min/1.73m^2^). It is expected that the site, weight and eGFR have the biggest impact on the outcome measures. First, the groups should be similar regarding renal function because this may affect outcome. It can be argued that in patients with a reduced renal function, physicians are more careful with the amount of administered contrast. Thus, by using the eGFR as a stratification factor, this bias will be minimized. Second, the radiation dose is taken into account, which is dependent on the patients’ weight. Therefore, stratification on weight is important. Third, it is not preferable to have one of the sites primarily performing the interventions with the 3D fusion technique and vice versa, since that would influence the user experience and is possibly also be related to the amount of contrast volume that is administered and the radiation dose that is used. Hence, these stratification factors were chosen to keep the distribution between the groups equal. Owing to the nature of the study, randomization will not be blinded for patients or physicians.

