### Sample size calculation and statistical analysis

The sample size was calculated using a two-tailed t-test with null hypothesis *E(D) = 0* (no difference between the groups) and alternative hypothesis *E(D) ≠ 0* (groups are different). A type I error (*α*) of *0.05* with z-value *Z*_*α*_ ≈ *1.96* was accepted resulting in1$$ {Z}_{\alpha }=\sqrt{N}\frac{D}{\sigma_D}>1.96 $$with *N* the sample size and *σ*_*D*_ the expected standard deviation. When assuming the alternative hypothesis is true *E(D) = τ* the power (*π*(*τ*)) can be calculated by2$$ \pi \left(\tau \right)=1-\Phi \left(1.96-\sqrt{N}\frac{\tau }{\sigma_D}\right) $$with Φ being the Phi coefficient. When accepting a power of at least 0.90, the alternative hypothesis for *E(D) = τ* can be estimated by

3$$ \pi \left(\tau \right)=1-\Phi \left(1.96-\sqrt{N}\frac{\tau }{\sigma_D}\right)>0.90. $$

Alternatively, this can be written with as4$$ \Phi \left(1.96-\sqrt{N}\frac{\tau }{\sigma_D}\right)<0.10. $$

For a type II error of 0.1, the z-value (*Z*_*β*_) becomes approximately *1.28*5$$ \sqrt{N}\frac{\tau }{\sigma_D}>1.96+{Z}_{\beta }=1.96+1.28\approx 3.24 $$

Given that half of the proportion of the study patients is randomized into the control group (*q*_0_ = 0.5) and the other half in the study group (*q*_1_ = 1 − *q*_0_ = 0.5), the sample size (*N*) can then be estimated by6$$ N>\left(\frac{1}{q_0}+\frac{1}{q_1}\right){\left(\frac{3.24}{\tau }{\sigma}_D\right)}^2 $$

Based on earlier research [9], we expect that *τ* = 20 mL of administered contrast volume may be reduced with the use of the 3D image fusion technique by reducing the number of contrast runs by at least two. Full-strength iodinated contrast is diluted 50:50 with a normal saline solution because a lower concentration of iodinated contrast agent has been shown not to compromise image quality during DSA of PAD patients [10]. To achieve a reduction of 20 mL per procedure with a mean volume of 60 mL and corresponding standard deviation of *σ*_*D*_ = 30 mL, the sample size *N* becomes a total of 96 patients. Therefore, 48 patients will be needed in each group. Adjusting for an anticipated loss to follow-up of 10%, the total sample size will be 106 patients. An interim analysis will be performed halfway through, after inclusion of the first 40 patients, to assess the efficacy of the 3D fusion technique compared to the control group.

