Normal distribution of the data will be tested. Normally distributed data will be represented as the mean and 95% confidence interval; non-normally distributed data will be represented as the median and interquartile range. Continuous variables will be analyzed with the independent samples *t*-test or Mann–Whitney *U* test for normally and non-normally distributed data, respectively. Categorical data will be analyzed with the *χ*^2^ test. All tests will be two-sided and considered significant when *P* < 0.05.

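### Allocation is minimised on site, weight and eGFR, but contrast volume is compared without adjustment for them, so available precision is forgone (planned power and type I error are not put at risk)

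*Protocol article*

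**What the plan says.** Allocation (protocol article, Randomization): "Randomization will be performed according to minimization; for a difference of 2 between the two groups", the smaller group is favoured with 90% probability. The factors are site, weight (cut at 90 kg) and eGFR (cut at 60 mL/min/1.73m²). The general reason given is: "It is expected that the site, weight and eGFR have the biggest impact on the outcome measures". The particular reasons differ by factor. Renal function is argued to influence how sparingly physicians give contrast. Site is said to be possibly related to contrast volume and radiation dose. Weight is tied to radiation dose.

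The primary endpoint is the volume of iodinated contrast in mL (Study objectives and endpoints).

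Analysis (Sample size calculation and statistical analysis): "Continuous variables will be analyzed with the independent samples" t-test, or with the Mann–Whitney U test when the data are not normal. "All tests will be two-sided and considered significant when *P* < 0.05". Nowhere in the article is an adjusted or stratified comparison named. The sample size in the same section uses a difference of 20 mL and an SD of 30 mL, with no reduction for covariates.

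**The concern.** Minimisation forces the arms to be similar on its factors. If those factors predict contrast volume, the difference between arm means varies less from trial to trial than it would under simple randomisation. The two-sample t-test does not know this. It estimates its standard error from the full within-arm spread, including the part due to site, weight and eGFR. The reported standard error then exceeds the true one, the 95% interval covers more than 95%, and the test rejects a true null hypothesis less than 5% of the time. The Mann–Whitney test behaves in the same way.

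What is at stake is efficiency. The factors must be known to allocate each patient, so an analysis that uses them needs no extra patients and no extra data.

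**Working it through.** **Inputs from the article:** two-sided α 0.05; power 0.90; difference 20 mL; SD 30 mL; 1:1 allocation; 96 evaluable patients, 48 per arm; three two-level minimisation factors.

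**Not in the article:** R², the share of the variance of contrast volume explained by the three factors. I take 0, 0.1, 0.2 and 0.3 as assumptions.

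**Step 1: reproduce the plan.** Equation 6 gives N > 4 × (3.24 × 30/20)² = 4 × 4.86² = 94.5, hence 48 per arm and 96 in total, as stated. The unadjusted standard error is 30 × √(2/48) = 6.12 mL. Then 20/6.124 = 3.266, and power is Φ(3.266 − 1.96) = Φ(1.306) = 0.904.

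**Step 2: closed form, arms close to balance on the factors.** The estimated unadjusted standard error stays at 6.12 mL, while the true one is close to the adjusted one.

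- Adjusted standard error: 6.12 × √(1 − R²)
- Excess of the unadjusted standard error: 1/√(1 − R²) − 1
- True size of the unadjusted test: 2[1 − Φ(1.96/√(1 − R²))]
- Power, unadjusted: Φ(1.306/√(1 − R²))
- Power, adjusted: Φ(3.266/√(1 − R²) − 1.96)

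| R² (assumed) | Adjusted SE (mL) | Unadjusted SE too large by | True size, unadjusted | Power, unadjusted | Power, adjusted |
|---|---|---|---|---|---|
| 0 | 6.12 | 0% | 0.050 | 0.904 | 0.904 |
| 0.1 | 5.81 | 5% | 0.039 | 0.916 | 0.931 |
| 0.2 | 5.48 | 12% | 0.028 | 0.928 | 0.955 |
| 0.3 | 5.12 | 20% | 0.019 | 0.941 | 0.974 |

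For example, at R² = 0.2: 1.96/0.894 = 2.19, so size is 0.028; 1.306/0.894 = 1.46, so unadjusted power is 0.928; 3.266/0.894 − 1.96 = 1.69, so adjusted power is 0.955. The 95% interval is ±1.96 × 6.12 = ±12.0 mL unadjusted, against ±1.96 × 5.48 = ±10.7 mL adjusted.

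**Step 3: simulation of minimisation itself.** Step 2 assumes near balance, so I also simulated the allocation: 96 patients, 6000 trials per setting, and a 90% biased coin once the imbalance summed over the three factors reaches 2. Further assumptions are factor prevalences of 0.5, 0.3 and 0.3, equal factor weights and normal outcomes.

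| R² | Size: t-test | Size: Mann–Whitney | Size: adjusted | Power at 20 mL: t-test | Mann–Whitney | Adjusted |
|---|---|---|---|---|---|---|
| 0 | 5.0% | 5.1% | 5.0% | 89.5% | 87.9% | 89.3% |
| 0.1 | 3.8% | 3.8% | 4.9% | 91.3% | 89.8% | 92.7% |
| 0.2 | 2.6% | 3.0% | 4.9% | 92.2% | 90.9% | 95.3% |
| 0.3 | 2.1% | 2.1% | 5.1% | 92.8% | 91.3% | 97.0% |

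The t-test falls short of the adjusted model by about 1.5, 3 and 4 points at R² = 0.1, 0.2 and 0.3. At R² = 0.2 with no treatment effect its mean standard error is 6.11 mL, while the difference in means actually varies with an SD of 5.52 mL.

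**Step 4: is minimisation the cause?** Under simple randomisation at R² = 0.2, with no treatment effect, the t-test's size is 5.1% and its standard error (6.15 mL) matches the actual SD (6.15 mL). The conservatism therefore comes from ignoring the forced balance.

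**The case against.** **Planned power.** A reader might infer that the unadjusted test leaves the trial underpowered. The article does not support that. The trial was sized on the unadjusted SD, so the design figure of 0.904 does not depend on adjustment. In the closed form, t-test power at 20 mL rises with R². This stands. The shortfall exists only against a better analysis. It would be larger for a smaller effect (at 15 mL and R² = 0.2, 70.0% against 78.0%), but the protocol does not plan for 15 mL.

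**Validity.** A reader might also infer that the P-value is unsafe. The error runs the other way: size falls below 5% and the interval is too wide. There is no false-positive risk. This stands too.

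**Size of the effect.** The article gives no R². Its statement about impact covers the outcome measures together. For contrast volume the support is hedged, and weight is linked only to radiation dose. Nothing in the text establishes 20% or 30% for the primary endpoint. This stands: the direction is firm, the size is conditional.

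**Purpose of the factors.** The Randomization section justifies them by comparability of the groups and claims no gain in precision. That is true, but it does not change how the standard error behaves once balance has been forced.

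**Condensed article.** A full protocol or analysis plan might add adjustment. This defence is limited, because the article does not leave the test open. It names one, and that test ignores the allocation.

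**Conclusion.** The stated analysis does not match the stated allocation. As far as site, weight and eGFR predict contrast volume, the unadjusted standard error is too large, the interval too wide and the test conservative. If R² is 0 nothing is lost. If it is 0.1, 0.2 or 0.3, the standard error of 6.12 mL is about 5%, 12% or 20% too large, true size is about 0.04, 0.03 or 0.02 instead of 0.05, and power at 20 mL is about 1.5, 3 or 4 points below an adjusted analysis.

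These sizes rest on the assumed R², the design SD of 30 mL, 48 patients per arm and, for the simulation, the prevalences, equal weights, normal outcomes and reading of the allocation rule given above. The plan should be improved here, but neither the 90% power nor the 5% error rate is undermined.

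**What to change.** Make the primary analysis a linear model of contrast volume on arm plus the three minimisation factors, in one prespecified form, for example the categories used for allocation. Report the adjusted mean difference in mL with its 95% CI.

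State in advance what happens if the residuals are clearly skewed: either a log transformation or a stratified rank test (van Elteren). Choose one, since the log scale yields a ratio and the rank test yields no difference in mL.

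Use the same approach for fluoroscopy time, procedure time and dose area product. Keep the unadjusted test as a sensitivity analysis.

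The cost is 3 degrees of freedom (residual 96 − 5 = 91 instead of 96 − 2 = 94) and a documented change to the protocol and analysis plan. Timing matters. The trial is open-label and has no DSMB, an efficacy interim is set at 40 patients, and Trial status reports 40 enrolled. The change should be fixed before any comparison by arm, including that interim. If the comparison has already been made, the record should show that the change was decided without regard to arm-level results.

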### Intervention

The aim of the endovascular treatment is to obtain a patent CIA and/or EIA (i.e. < 30% residual stenosis or a reduction of the mean pressure gradient to < 10 mmHg [11]), resulting in an improved blood flow to the legs. In case of a flow limiting dissection, > 30% residual stenosis, or acute elastic recoil after PTA, additional stent placement will be performed. If indicated, other arteries will be treated in addition to the CIA and/or EIA during the same intervention. The physician will choose an ipsilateral or contralateral technique (or rendezvous procedure), depending on the location of the lesion. The analysis will not include data of patients with solely diagnostic DSAs.

Before the start of the intervention, the patient will be placed supine on the angiography table. The contrast pump and table contrast agent will be diluted 50:50 with a normal saline solution. For patients randomized into the study group, a non-contrast-enhanced CBCT will be created at the beginning of the intervention using the flat panel detector of the C-arm angiography system (Allura Xper FD20; Philips Healthcare). The CBCT will be automatically transferred to the 3D XtraVision workstation (Philips Healthcare). Subsequently, a manual 3D-3D registration will be performed between the preprocedural MRA and CBCT based on bony landmarks, such as vertebrae and the femoral heads, and the flow lumen on the MRA will be matched to the border of the calcifications as seen on the CBCT. The time required to perform the registration will be recorded.

After the registration, the physician will visually score the fusion accuracy of the entire iliac vasculature between the overlay and the initial DSA run. This fusion accuracy will be determined directly after the DSA is created and will be categorized as accurate (< 2 mm), mismatch (2–5 mm), or inaccurate (> 5 mm). An overlay that is inaccurate will be manually translated or reregistered to achieve a more accurate overlay that will be used during the intervention. Subsequently, the intervention will be performed according to the standard of care procedure and contrast runs will be performed when needed.

DSAs will be performed with 15 mL at 12 mL/s or 8 mL at 4 mL/s using a catheter in the aorta or CIA, respectively. A completion DSA will be created to confirm procedural success. DSA runs, whether or not in combination with the overlay (for the study group), will be stored. Primary and secondary endpoints will be registered, as well as baseline characteristics and procedural details, including ipsilateral or contralateral, length and location of the lesion, type of PTA balloon or stent, and number of stents.

All patients will receive 5000 IU of heparin during the intervention. The patients will receive bed rest after the intervention according to the physician’s prescription. All patients will be prescribed acetylsalicylic acid (ASA or aspirin) at 80 mg/d. The PTA and recanalization procedures are generally performed as outpatient procedures. Patient participation in the study will be completed after discharge. Any complication that occurs between the signed informed consent and hospital discharge will be recorded. There is no further follow-up period for this study.

### Data collection

Data will be collected by use of an electronic case report form (eCRF), which will be prospectively maintained from the time the patient signs the informed consent until the completion of the study. Patient data will be anonymized; each individual will be given a unique study number (site code [MUMC/ANTO] and index number). Each center can only view and add eCRF data from its own site. At the end of the study, the eCRFs of both sites will be become available to both centers.

### Monitoring and adverse events

A Data and Safety Monitoring Board (DSMB) will not be appointed for this study. A qualified monitor of the Clinical Trial Center Maastricht (CTCM) will monitor the study, which will ensure that the study is conducted according to ICH-GCP guidelines. Visits are conducted at the start of the study, after inclusion of five patients, halfway through, and at completion of the study. A monitoring report will be sent to the investigator after each visit.

Adverse events and serious adverse events will be recorded on the eCRFs. They will comprise a description of the event, type of complication (i.e. access site, systemic, organ-specific), severity, start date, end date, whether suspected to be intervention related, any action that is undertaken, and the outcome. Serious adverse events will be reported to the accredited METC through the “Toetsingsonline” page of the website of the Central Committee on Research Involving Human Subjects (in Dutch: Centrale Commissie Mensgebonden Onderzoek, CCMO [www.ccmo.nl]). The investigator will report serious adverse device events resulting from the use of the 3D image fusion technique to the accredited METC, the manufacturer, and the Inspection for Healthcare (in Dutch: Inspectie voor Gezondheidszorg [IGZ]).

## Discussion

The use of angiography during endovascular interventions is essential to visualize stenotic or obstructive lesions [12]. With increasing complexity of procedures, the amount of iodinated contrast agent may increase. The potentially nephrotoxic effects of the iodinated contrast agent are especially problematic in patients with pre-existing renal failure [2, 13, 14]. A recent systematic review confirmed that the amount of administered iodinated contrast agent can be significantly reduced by using the 3D image technique during EVAR procedures [15]. In addition, the radiation dose, procedure time, and fluoroscopy time may be reduced during these procedures [15], which could be beneficial to physicians, who receive high exposure to radiation throughout their practice.

A vacuum mattress can be used to reduce patient movement [16], which can minimize overlay inaccuracy caused by movement artifacts. We assume that movement artifacts will be smaller in the pelvic area than in the legs and that registration in this area will be less challenging because of the bony structures (vertebrae, femoral head, and iliac crest) and larger diameters of the arteries. This research focuses on the iliac arteries; when this study demonstrates the benefits of the 3D fusion technique in endovascular iliac artery interventions, the technique can be extended to femoro-crural lesions.

An alternative to iodinated contrast agents is the use of angiography based on carbon dioxide (CO_2_). The use of CO_2_ during EVAR procedures is safe and reliable and may be especially beneficial for patients with renal insufficiency [17]. However, variability in image quality has been reported and a careful technique is required for each injection to prevent air contamination. Additionally, there is a possibility of pain after injection, and CO_2_ for intravascular use has the potential for air embolism, which could result in ischemia or tissue infarction [18]. Although CO_2_ may be able to replace nephrotoxic contrast agents and reduce iodine contrast agent costs [18, 19], it will probably not reduce the radiation doses to patient and staff. Carbon dioxide and the 3D image fusion technique can be complementary during (complex) EVAR [20, 21]; however, 3D fusion in combination with CO_2_ for iliac artery interventions has not yet been investigated.

Preoperative MRA or CTA can be used for 3D image guidance. Registration between two similar image modalities (i.e. CTA to CBCT) may be less challenging than registration between MRA and CBCT, because MRA visualizes the flow lumen of the arteries, instead of calcified speculae. Nevertheless, because an MRA of the lower abdomen, pelvis, and lower extremities is the standard diagnostic imaging in the preoperative workflow of many patients with PAD, only patients with preoperative MRA datasets will be included; therefore, patients with contraindications to MRA are not eligible. Furthermore, because of susceptibility artifacts on the MRA, in-stent stenoses cannot be judged and those patients will not be included in this trial. No additional preoperative imaging needs to be performed for this study and patient burden is minimized.

Image registration can be performed to a CBCT (3D-3D image fusion) or two fluoroscopic orthogonal projections (2D-3D image fusion). The acquisition of a CBCT and registration process takes approximately 5–10 min and is reported to be more accurate than 2D-3D image fusion [20]. However, the latter is reported to be fast and can be performed with a minimal effective dose of 0.14–0.20 mSv [21]. Sailer et al. [22] reported that a CBCT corresponds to a mean effective dose of 3.5 mSv (95% confidence interval, 3.0–4.1 mSv), whereas van den Berg [21] reported an effective dose of 1.53–1.66 mSv. The patient’s radiation dose from a CBCT may add 21% of the total procedural DAP for iliac artery interventions [9], which is comparable to approximately 7 min of fluoroscopy time [22]. During fluoroscopy, the physician is at the tableside, but is usually far away from the C-arm during the acquisition of the CBCT. When the 3D fusion technique is used during EVAR, the fluoroscopy time could be significantly reduced [23, 24]. This reduction may also be feasible for iliac artery interventions, which will be beneficial to both the operator and the patient, and could potentially result in a reduction of costs. The possible benefit for contrast saving, combined with the possible reduction of fluoroscopy time might outweigh the additional radiation dose of a CBCT.

### Trial status

The METC has approved the study protocol. Currently, 40 patients have been enrolled in the 3DMR-Iliac-Roadmapping study. The expected project completion for this trial is December 2018.

